### Plans to promote participant retention and complete follow-up

Participants will be provided with contact details of the trial study team and will be encouraged to contact the team with any queries or concerns.

Participants who wish to withdraw from trial medication (IMP) will be asked to confirm whether they are still willing to attend the safety follow-up visits as per protocol for the duration of the trial. If participants are not willing to do this, consent will be sought for the trial team to access routine data collected from hospital/General Practitioner (GP) visits for the duration of the safety follow-up period.

### Data management

A specific data management plan has been created for the trial. Data will be entered in the eCRF platform to automatically create a protected audit trail for all data entries and changes.

Access to the trial eCRF platform will be password protected and electronic login credentials will be issued only to authorised individuals.

### Confidentiality

To protect the privacy and identity of trial patients, patients will be assigned a unique patient trial identifier upon enrolment. Only investigators and authorised staff at the trial site will be in possession of documents that link patient names to patient trial identifiers (ie, Informed Consent Form (ICF) and Patient Identification Log).

### Plans for collection, laboratory evaluation and storage of biological specimens for genetic or molecular analysis in this trial/future use

Populations of circulating lymphocytes in the blood of patients undergoing TR004 immunotherapy will be assessed for their phenotype and the production of cytokines including IFNγ, Tumour Necrosis Factor alpha (TNFα), IL-5, IL-10, IL-12, IL-13, IL-17, IL-18, IL-22, IL-23, IL-33, Granulocyte-macrophage colony-stimulating factor (GM-CSF) and oncostatin.

Peripheral blood will also be collected at various study visits to assess the levels of circulating regulatory T cells labelled with deuterium. Please refer to online supplemental table 2 section for more details.

24 punch biopsies will be taken from a combination of the ileum and the colon from each patient undergoing TR004 immunotherapy at screening and at week 8. Lymphocytes localised in the ileum and colon of patients undergoing TR004 immunotherapy will be assessed, and their phenotype and cytokine production will be compared with circulating lymphocytes to determine any differences or similarities between circulating and localised cells. Research stool samples collected during the trial will be sent for microbiome analysis after the end of the study.

## Statistical methods

### Statistical methods for primary and secondary outcomes

In view of the feasibility trial design and the numbers of patients, the statistical analysis approach will be a descriptive presentation of each patient’s data rather than the calculation of summary statistics.

### Interim analyses

Given this is a small feasibility study including a small cohort of only four patients, no formal interim analyses are planned. The study may be terminated prematurely by the sponsor, CI or regulatory authority on the basis of new safety information or for other reasons given by the DSMB, regulatory authority or ethics committee concerned. In the event of premature termination, the sponsor will notify the regulatory authorities within 15 days by providing a detailed written explanation. The CI will inform the research ethics committee (REC). The affected trial participants will also be informed promptly and appropriate follow-up visits will be arranged. No further participant data will be collected.

The clinical trial may be prematurely terminated for the following reasons:

Serious and/or persistent non-compliance with trial protocol.Non-compliance with ethical standards, regulatory requirements or GCP compliance.Findings uncovered during monitoring visits, audits or inspections that compromise patient safety or suitability of the site to act as a trial centre.Recommendation from DSMB.Failure to meet recruitment targets.

During the course of the study, any of the following events will trigger a pause in patient recruitment and an emergency review by the DSMB:

Death.DLT observed in two patients out of four.

In the event of emergency review by the DSMB, a substantial amendment will be submitted to the Medicines and Healthcare products Regulatory Agency (MHRA) for approval to restart the study.

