## Methods: participants, interventions and outcomes

### Trial design

This study is an open-label, first-in-human feasibility study of a single dose of TR004 in patients with moderate to severe CD. Four participants will receive a single dose of TR004. Participants will be dosed singly. Safety data will be collected for 5 weeks post administration and reviewed by the DSMB before proceeding to dose the next participant. All participants will be followed up to week 21 to collect further safety and exploratory efficacy data, with additional safety monitoring at 1 and 2 years post dose.

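### Early termination would stop all data collection, cutting short the safety follow-up of participants already infused

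*Protocol article*

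**What the plan says.** The rule is in the Interim analyses section. The grounds for stopping include safety: "The study may be terminated prematurely by the sponsor, CI or regulatory authority on the basis of new safety information". The listed reasons also include a DSMB recommendation, various forms of non-compliance, site unsuitability and "Failure to meet recruitment targets". On what then happens to participants, the text says "The affected trial participants will also be informed promptly and appropriate follow-up visits will be arranged", and the next sentence is "No further participant data will be collected". Nothing limits that sentence to participants not yet infused, to research samples, or to data other than safety data.

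The same section treats a death, or a DLT in two of four patients, differently: "any of the following events will trigger a pause in patient recruitment and an emergency review by the DSMB".

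Four other places describe what is to be observed after infusion:

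- **Trial design:** "All participants will be followed up to week 21 to collect further safety and exploratory efficacy data". Longer-term safety checks, 1 year and 2 years after the infusion, are promised in the same place.
- **Secondary endpoints:** adverse events that are not DLTs, and those arising after week 5, are to be described.
- **Adverse event reporting and harms:** adverse events are recorded from consent to the week 21 visit. From then to week 104 only SUSARs are reported.
- **Plans to promote participant retention and complete follow-up:** a participant who withdraws from trial medication is asked to keep attending safety visits. If unwilling, the participant is asked to consent to use of routine hospital and GP data.

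**The concern.** TR004 is a single infusion of living cells, so closing the trial does not end a treated participant's exposure. The background section cites earlier work in diabetes, with a similar approach, in which transferred cells were detectable in blood for up to 1 year. That is not evidence on TR004, but it is the article's own reason to expect that late observation could matter.

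Read literally, the termination rule means that a trial closed on safety grounds would stop recording how toxicities resolve, whether other infused participants have late events, and whether anything appears at 1 or 2 years. The observation would be cut short because of the outcome being observed. With four participants and patient-by-patient description, nobody else can supply the missing information. The same cut would follow a stop for slow recruitment, where the article gives no safety reason for it.

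The rule also has an odd consequence. A participant willing to continue in a terminated trial would contribute less safety data than one who chose to withdraw.

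**Working it through.** The article derives no figure on this point, so there is none to reproduce. The check has two parts.

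**1. The provisions side by side**

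| Provision | Section | If the termination rule is followed |
|---|---|---|
| Follow-up of all participants to week 21 | Trial design | Ends at the stop |
| Safety monitoring at 1 and 2 years | Trial design | Not done for anyone short of those times |
| Description of events after week 5 | Secondary endpoints | Incomplete, or absent for the latest participant |
| Adverse events to week 21, SUSARs to week 104 | Adverse event reporting and harms | No continuing data to support either |
| Safety visits, or routine records with consent, after withdrawal | Participant retention and follow-up | Not offered after termination |

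**2. How much follow-up would be lost**

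Inputs from the article: planned follow-up of 21 weeks with full adverse event recording and 104 weeks in all; participants dosed singly; "Safety data will be collected for 5 weeks post administration and reviewed by the DSMB before proceeding to dose the next participant". The spacing between infusions is not given beyond that 5-week minimum. Spacing is therefore an assumption: 5 weeks (the minimum, with no time allowed for DSMB review), and 12 and 26 weeks as a range. The time of termination is also assumed.

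If termination comes d weeks after the k-th infusion and spacing is s, participant i has been followed for (k − i) × s + d weeks. The share lost to horizon H is the sum over participants of max(0, H − follow-up), divided by k × H.

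*Termination 5 weeks after the second infusion, s = 5.* Follow-up is 10 and 5 weeks, 15 in total.

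- To week 21: planned 2 × 21 = 42; lost 42 − 15 = 27; 27/42 = 64%. Neither participant reaches week 21.
- To week 104: planned 2 × 104 = 208; lost 208 − 15 = 193; 193/208 = 93%.

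*Termination 5 weeks after the fourth infusion.* Planned 4 × 21 = 84 and 4 × 104 = 416 participant-weeks.

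| Spacing (weeks) | Follow-up reached (weeks) | Lost to week 21 | Lost to week 104 |
|---|---|---|---|
| 5 | 20, 15, 10, 5 | 34/84 = 40% | 366/416 = 88% |
| 12 | 41, 29, 17, 5 | 20/84 = 24% | 324/416 = 78% |
| 26 | 83, 57, 31, 5 | 16/84 = 19% | 240/416 = 58% |

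In none of the scenarios tried (termination 1 or 5 weeks after the first to fourth infusion, at each spacing) does any participant reach week 104.

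**Effect on the primary endpoint.** The DLT window is 5 weeks, and the next participant is not dosed until those 5 weeks have been reviewed. At any stop, at most one participant is inside the window; earlier DLT assessments are complete.

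**The case against.** Several points count against a stronger reading.

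- **A reader might infer that a safety stop would wipe out the trial's safety data.** The documents do not support that. The sentence concerns further data only, and nothing says that data in hand are deleted or left unreported. The primary endpoint is largely protected by the dosing sequence. This stands.
- **A reader might infer that two DLTs or a death would themselves switch off data collection.** They would not. They pause recruitment and bring an emergency DSMB review, and restart is possible after an amendment. The data stop needs a further decision to terminate. This stands, although new safety information and a DSMB recommendation are both named grounds, so the path exists.
- **A reader might take the two neighbouring sentences, on arranging visits and on collecting no data, as a flat contradiction.** They can be reconciled if the visits are for care only; participants receive their IBD care at the same Trust. The sponsor may also have meant only research data, but the text does not say so. The firmer conflict is with the other sections.
- **The 93% treats every week to 104 as equal.** After week 21 the article plans two monitoring points and SUSAR reporting only. The 64% to week 21 describes the loss of full adverse event recording better, and both figures depend on assumed timing.
- **The article condenses a fuller protocol.** This has little force here, because the sentence is an unqualified statement and not an omitted detail.
- **Analysis is descriptive, so no planned estimate is biased.** True, but the description itself would be incomplete.

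**Conclusion.** The concern holds as one of truncated safety follow-up. As written, the termination rule cannot be squared with the follow-up in Trial design, the secondary endpoint on later events or the adverse event and SUSAR periods, and it is stricter than the withdrawal provision. It takes effect only after a decision to terminate, and it leaves collected data and nearly all DLT assessments intact.

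The size depends on when termination falls and on spacing that the article does not give. At the minimum 5-week spacing, termination 5 weeks after the second infusion loses 64% of participant-weeks to week 21 and 93% to week 104. Five weeks after the fourth infusion the losses are 19% to 40% and 58% to 88% over the spacings tried. The week 104 figures should be read with the sparse monitoring after week 21 in mind.

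For a first-in-human cell product whose stated aim is preliminary safety, this is worth correcting. Observations not made after a stop may not be recoverable.

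**What to change.** Replace the sentence with wording to this effect: *On premature termination no further participant will be recruited or infused. For participants already infused, safety data will continue to be collected and reported on the schedule in this protocol: adverse events to week 21, then SUSARs and the 1- and 2-year safety monitoring to week 104. Where a participant declines visits, consent will be sought to use routine hospital and GP records.*

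This keeps to the article's existing reporting periods and to the consent condition already applied to withdrawals. Trial design, the retention and follow-up section, Interim analyses, and Adverse event reporting and harms should be aligned with it. If the present sentence was meant to cover only research samples or efficacy data, it should say so.

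The cost is an amendment touching those sections, and a database and safety reporting kept open for about four participants whose visits are already planned. Termination because the single site is unsuitable or non-compliant would need its own arrangement, since collection there might not be able to continue.

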### Methods for additional analyses (eg, subgroup analyses)

Not applicable as this is a small trial with only four patients, there will be no subgroups.

### Methods in analysis to handle protocol non-adherence and any statistical methods to handle missing data

Not applicable as the treatment will be given as a single dose, so protocol non-adherence will not be an issue.

### Plans to give access to the full protocol, participant-level data and statistical code

The full protocol and participant-level dataset will be available on request.

## Oversight and monitoring

### Composition of the coordinating centre and trial steering committee

The Trial Management Group (TMG) is led by [name], the CI for this study. The group will include the CI, statisticians, clinical trial manager, project manager and representatives of the other teams involved in the delivery of the trial, including the GMP unit, laboratories, data management and the CRF. The TMG will be responsible for the day-to-day management of the trial activities and will meet on a regular basis to discuss any trial-related activities or issues.

The Trial Steering Committee (TSC) will provide advice for the conduct of the trial. It will comprise an independent chair and at least two other members. The TSC members will meet on an ad hoc basis to discuss trial status, recruitment progress and any other relevant issues, and provide recommendations to the TMG/sponsor.

### Composition of the data monitoring committee, its role and reporting structure

A DSMB, which is independent from the sponsor, will be constituted prior to study opening. The DSMB charter will detail membership and terms of reference. The DSMB members will be independent and supported by the trial statistician. In order to ensure patient safety throughout the conduct of the trial, the DSMB will review and evaluate accumulated safety data, study conduct and progress. The DSMB will make the decisions about the continuation, modification or termination of the study.

The DSMB members will convene at defined time points stated in the DSMB charter.

A DSMB meeting would also be triggered if specific safety events occurred (see below).

The DSMB meeting will take place:

If a DLT is observed in two patients out of four.If death of a patient infused with TR004 occurs.Or at any other time deemed necessary by the DSMB chair.

### Adverse event reporting and harms

Adverse events (AEs) will be recorded and graded according to the Common Terminology Criteria for Adverse Events.^38^ AEs (including serious adverse events) will be recorded from study entry (once the patient has consented) to week 21 visit. During the safety follow-up period (from end week 21 to week 104), only Suspected Unexpected Serious Adverse Reactions (SUSARs) will be reported.

The delivery of the co-sponsors’ responsibility for pharmacovigilance (as defined in Regulation 5 of the Medicines for Human Use (Clinical Trials) Regulations 2004) has been delegated to the King’s Health Partners Clinical Trials Office (KHP-CTO). The KHP-CTO will report SUSARs to the regulatory authority, the MHRA. The CI and KHP-CTO (on behalf of the co-sponsors) will submit a Development Safety Update Report relating to this trial IMP to the MHRA and REC annually. The CI will submit annually to the main REC an Annual Progress Report.

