### Outcomes

#### Primary clinical endpoint

Rate of dose-limiting toxicities (DLTs) occurring within 5 weeks post infusion of TR004.

Feasibility endpoint

Amount of TR0004 manufactured per patient.Number of participants recruited within the duration of the trial.Number of study visits completed.Responses to items in questionnaires or surveys exploring the experience of the participants, trial team and DSMB members. This will not form part of the final trial report. Qualitative data collection and any data analysis will be separate from the trial.

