#### Secondary endpoints

Assessment of clinical response:Disease Activity Score (CDAI/PRO-2).Biomarkers analysis (CRP, FCP).Mucosal healing response (SES-CD).Assessment of immunological response—in blood and intestinal LP:Numbers and functions of Tregs.Measurement of deuterium-enriched cells.Cytokine levels.Comparison of circulating and localised cells to determine differences and similarities.Description of non-DLT adverse events and those occurring beyond week 5.

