### Participant timeline

Trial participants will be reviewed and assessed throughout the trial from Screening to Week 104. Clinical blood tests will be performed throughout the duration of the study, and blood samples for translation research will be collected up to week 21 post infusion. Regular visits will be scheduled up to week 8, with follow ups scheduled on week 16 and week 21 thereafter. Please refer to online supplemental tables 1A,B section for more details.

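### After week 21 the protocol limits safety reporting to SUSARs, which does not match its 1- and 2-year safety monitoring, its open-ended adverse event endpoint or its death trigger

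*Protocol article*

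**What the plan says.** The section on adverse event reporting and harms sets two windows. In the first, "AEs (including serious adverse events) will be recorded from study entry (once the patient has consented) to week 21 visit". In the second, "During the safety follow-up period (from end week 21 to week 104), only Suspected Unexpected Serious Adverse Reactions (SUSARs) will be reported".

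Other sections of the article describe a wider safety commitment:

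- Trial design follows all participants to week 21, "with additional safety monitoring at 1 and 2 years post dose". The abstract says the same.
- Participant timeline: "Trial participants will be reviewed and assessed throughout the trial from Screening to Week 104", and "Clinical blood tests will be performed throughout the duration of the study".
- Secondary endpoints: "Description of non-DLT adverse events and those occurring beyond week 5". No end date is given.
- The DSMB section lists as a reason to meet: "If death of a patient infused with TR004 occurs". The section on interim analyses also makes a death during the study a reason to pause recruitment and hold an emergency review. Neither place limits the trigger by causality, expectedness or time since infusion.

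**The concern.** A SUSAR must be serious, suspected to be related, and unexpected. If only such events count after week 21, a late malignancy, infection, Crohn's admission or death enters the safety data only after someone has judged it both related and unexpected. The study has four participants, no comparator and open-label treatment, so those judgements rest on single cases with nothing to compare them against. They should be made on a recorded event, not decide whether the event is recorded.

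The article's own background makes the later period relevant. It cites earlier work in diabetes in which transferred cells were detectable in blood for up to 1 year. It also warns that transferred cells able to make effector cytokines could do harm by contributing to Crohn's disease. A late disease flare with admission could be such a harm, yet it could easily be put down to the underlying disease.

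At stake is what the final report can say about late safety. Preliminary safety is the stated objective, and the results are meant to inform a larger trial.

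**Working it through.** The plan gives no figure of its own on this point, so there is none to reproduce. The check is window arithmetic and a comparison of sections.

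**Inputs.** Full recording to week 21, SUSAR-only reporting from week 21 to week 104 (adverse event reporting and harms). Endpoint starting after week 5 (secondary endpoints). Participants dosed singly, with 5 weeks of safety data reviewed before the next infusion (trial design). Start of inclusion 8 August 2022 and estimated primary completion 31 March 2024 (trial status).

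**1. Length of the restricted window.** 104 − 21 = 83 weeks; 83/104 = 79.8% of post-dose follow-up.

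**2. The adverse event endpoint.** No end date is given. Assuming that it runs to the end of follow-up, it spans 104 − 5 = 99 weeks. Full recording covers 21 − 5 = 16 of these, 16/99 = 16.2%. The other 83 (83/99 = 83.8%) are SUSAR-only. These are shares of calendar time, not of events.

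**3. Sections compared for weeks 21 to 104.**

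| Commitment | What it needs | What the harms section provides |
|---|---|---|
| Safety monitoring at 1 and 2 years | A defined set of events to record | SUSARs only |
| Adverse events after week 5 | Adverse events up to some end date | SUSARs only |
| DSMB review on any death | Every death of an infused participant | Deaths that qualify as SUSARs; no stated route for others |

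**4. Could the restricted window overlap with dosing?** At the minimum spacing of 5 weeks, the fourth infusion falls 3 × 5 = 15 weeks after the first, and participant 1 is still under full recording. Participant 1 is past week 21 at the fourth infusion once the three intervals average more than 21/3 = 7 weeks. Start of inclusion to estimated primary completion is 601 days, or 85.9 weeks, so this is possible. As a scenario only: if primary completion is the last participant's week 5, the last infusion is on 25 February 2024. Anyone infused before 1 October 2023 (21 weeks earlier) would then be SUSAR-only on that day. The article gives no infusion dates.

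**5. What share of serious events would still be reported?** Share = P(suspected related) × P(unexpected, given related). The article gives neither probability. Assuming 0.1 to 0.9 for the first and 0.5 to 1.0 for the second, the share runs from 0.1 × 0.5 = 5% to 0.9 × 1.0 = 90%. The range is too wide to support any statement about how many events would be missed.

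**6. Effect of the remedy.** Recording deaths and serious adverse events to week 104 raises the coverage of serious events after week 5 from 16 of 99 weeks to 99 of 99. No sample size or error rate changes.

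**The case against.** The strongest reply is that the sentence is a reporting rule and not a rule about what is written down. The paragraph that follows uses the same verb for sending SUSARs to the regulator. Participants are still seen, with clinical blood tests, to week 104. All are registered with the same Trust for their Crohn's care. Those who withdraw and decline visits are asked to consent to use of routine hospital and general practice data. The death trigger is worded independently of SUSAR status. The article also condenses a full protocol and refers to supplementary visit tables and a DSMB charter, which may hold the detail. The DSMB reviews each participant's 5 weeks before the next infusion and can meet whenever its chair sees need, and annual safety reports go to the regulator and the ethics committee.

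Much of this stands, and it rules out several stronger readings that a reader might infer:

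- That the DSMB cannot learn of a late death. The trigger has its own wording and the team stays in contact with participants. What is lacking is a stated route for a death that is not a SUSAR.
- That late events are never captured. The article does not say that nothing is documented at the 1- and 2-year contacts.
- That most serious events are lost. The document gives no rates, and the 80% is a share of weeks.
- That dosing did continue while earlier participants were SUSAR-only. The dates show only that it could.
- That an unblinded investigator decides causality. The study is open-label, but the article does not say who judges.

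The reply does not remove the mismatch. The sentence just before closes the recording of adverse events, serious ones included, at week 21, and the next confines what follows to SUSARs. That is a stated restriction, not a detail left to another document, and it sits beside three commitments that are wider.

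**Conclusion.** The concern holds in limited form. The harms section closes the recording of serious adverse events at week 21 and restricts 83 of 104 post-dose weeks (80%) to SUSARs. In that period, deaths and serious adverse events judged unrelated or expected have no stated recording route. This does not match the promised long-term safety monitoring, the adverse event endpoint without an end date, or the unrestricted death trigger. A finding of no late safety signal could partly reflect non-collection that depends on single-case causality judgements in an uncontrolled study.

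The limits are equally clear. The primary endpoint, "Rate of dose-limiting toxicities (DLTs) occurring within 5 weeks post infusion of TR004", lies wholly inside the full recording window. The two-DLT trigger and the recording of adverse events from week 5 to week 21 are also unaffected. The number of events missed cannot be estimated, and overlap with dosing is possible but not shown.

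The conclusion rests on reading the two sentences of the harms section as written. The figures for the endpoint also assume that it runs to week 104.

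**What to change.** Amend the section on adverse event reporting and harms, and bring the related sections into line:

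1. Record all deaths and all serious adverse events to week 104 for every infused participant, whatever their judged causality or expectedness. Collect them at the existing 1- and 2-year contacts and from routine records. SUSAR reporting to the regulator continues as now.
2. State that any death of an infused participant, at any time in the study, is passed to the DSMB, so that the trigger has a data route.
3. Give the endpoint of adverse events after week 5 an end date that matches: all adverse events to week 21, serious adverse events and deaths to week 104.

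The cost is an amendment to the section and one added case report form page for about four participants, at contacts already planned. The one drawback is some extra processing of serious adverse events, for example for admissions due to Crohn's disease.
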